## Abstract

**Background:**

Most psychiatric disorders in childhood and adolescence cause impairment in academic performance. Early interventions in school are thought to reduce the burden of disorder and prevent chronicity of disorder, while a delay in reachable help may result in more severe symptoms upon first time presentation, often then causing upon first-time presentation immediate need of inpatient care.

**Methods:**

The study aims at reducing hospitalization rates and increasing social participation and quality of life among children and adolescents by establishing collaborations between schools, mental health care services and youth welfare services. CCSchool offers children and adolescents, aged six to 18 years, who present with psychiatric problems associated to school problems, a standardized screening and diagnostic procedure as well as treatment in school if necessary. Students can participate in CCSchool in three federal states of Germany if they a) show symptoms vindicating a mental health diagnosis, b) present with confirmed school problems and c) have a level of general functioning below 70 on the children global assessment of Functioning (C-GAF). Intervention takes place in three steps: module A (expected *n* = 901, according to power calculation) with standardized diagnostic procedures; module B (expected *n* = 428) implies a school-based assessment followed by a first intervention; module C (expected *n* = 103) offering school-based interventions with either four to six sessions (basic, 80% of patients) or eight to 12 sessions (intensive, 20% of patients).

Primary aim is to evaluate the effectiveness of CCSchool, in reducing the need of hospitalization in children with mental health problems. The analyses will be conducted by an independent institute using mainly data collected from patients and their caregivers during study participation. Additionally, claims data from statutory health insurances will be analysed. Relevant confounders will be controlled in all analyses.

**Discussion:**

Evaluation may show if CCSchool can prevent hospitalizations, enhance social participation and improve quality of life of children and adolescents with mental health problems by providing early accessible interventions in the school setting.

**Trial registration:**

Deutsches Register Klinischer Studien, Trial registration number: DRKS00014838, registered on 6th of June 2018.

## Background

Children and adolescents with any kind of disability, including children and adolescents with mental health disabilities, need good medical care all their life. Prevalence of psychiatric disorders in childhood and adolescence is high, ranging between 10 and 20% [1, 2]. More than 50% of these children and adolescents remain mentally impaired in adulthood [3–5, 6]. Once a severe mental health disease occurs, it tends to become chronic and may need repeated hospitalizations affecting daily life and social integration. It has been shown that mental health problems in children and adolescents subsequently not only contribute to lower achievements in education but bear an increased rate of health risk behaviour such as self-harm or suicidal behaviour [7] – issues that have a huge impact on later quality of life in adulthood. Thus, early diagnosis and adequate treatment in childhood mental health disorders are crucial for prevention of future persistence of disease. However, children and adolescents often experience considerable barriers accessing mental health services (e.g. lack of knowledge of mental health problems among care givers, difficult referral procedures, long distances and lack of transportation, especially in rural areas) [8, 9].

As children usually spend a considerable amount of time in school, schools have been referred to in the past as “the primary health care system for children” [10]. Hence, it is not surprising that in 70% of the cases schools indicate problematic behaviour and become thereby for the children and adolescents the main gate of entry into the mental health care system [11, 12]. Once having been seen by a psychiatrist early interventions in school may reduce the burden of disorder and help prevent chronicity of mental health problems, while on the other hand a delay in help may result in more severe symptoms when the child/adolescent finally presents. It is therefore of high importance to develop, implement and evaluate possible easily accessible pathways for provision of psychiatric care for children and adolescents with mental health problems.

Offering a low threshold school-based intervention in schools may promote a positive attitude towards mental health treatment among children and adolescents [13]. School may therefore not only be the ideal place for early detection of disease but also should be the place for early professional intervention [14]. Evidence from countries where school-based interventions have already been implemented, shows that relevant programs yield significant positive effects on students’ emotional well-being and behavior [7]. Also additional benefits in the treatment of children with mental health problems have been shown for treatments combining parental training with child or adolescent group-cognitive-behavioural-therapy (CBT) in school [6]. Cossu et al. [15] summarized in a review that school-based intervention programs can reduce symptoms of almost all mental disorders. In a recent study by Sanchez et al. [16], school-based services yielded a small-to-medium effect in decreasing mental health problems. The largest effects were found for targeted interventions, followed by selective prevention. Mental health services targeting externalizing problems were shown to be most effective when they were integrated in students’ regular academic schedule [16].

However, in the past decades, continuum of care between the school system, youth welfare system and mental health care services have not been existent in Germany. Reimbursement for psychiatric outreach work was not provided. In the absence of intensive outreach programs, rates of admission to inpatient services among children and adolescents in need of intensive psychiatric treatment were then rather high, while thresholds to use inpatient programs were inadequately lowered, alternative treatment options are lacking [17, 18]. Between 2007 and 2014 inpatient admissions in child and adolescent psychiatry in Germany increased by 38%, while the average duration of stay reduced only by 14%, resulting in an overall increase of inpatient beds needed by 17%. As a consequence transfer of inpatient-treatment effects to school and family surroundings is difficult, diminishing the chances for long-term effects and leading to increasingly often costly and frustrating “revolving door effects” with patients moving back and forth between in- and outpatient settings. On the other hand mental health treatments in natural surroundings (school, family) have been shown to acchieve more stable treatment effects over time. In those settings, relevant problems can be treated where they arise, involving school and family members alike [19–23].

On the 1st of January 2017 the “Act for further development of healthcare and reimbursement of psychiatric and psychosomatic services” (PsychVVG – “Gesetz zur Weiterentwicklung der Versorgung und der Vergütung für psychiatrische und psychosomatische Leistungen”) came into effect in combination with § 115d [24] in Volume V of the German Social Security Code (SGB V). A milestone in provision of care has been laid and the tide has turned: It is now possible for hospitals in Germany to offer continuum of care in form of outreach treatments to patients with mental health issues [25].

CCSchool aims to implement and evaluate a comprehensive, innovative outreach program, which - if effective - may later find its’ way into routine care. CCSchool focusses on offering early diagnostic and if necessary school-based interventions in a standardized procedure. The evaluation of CCSchool will answer the following research questions by comparing patients, who take part in CCSchool (intervention group), to patients in standard care (control group):Will - once continuum of care has been established in schools - the number and duration of inpatient and day-patient treatments in children and adolescents with mental health problems that manifest in school decrease?Will participation and integration of a child/adolescent with mental health issues and school problems improve when offering an adequate treatment on site (within schools)?Will quality of life for the patient and family be improved significantly in CCSchool intervention groups?

CCSchool is supported by a grant from the Innovation funds of the Federal Joint Committee of the Federal Republic of Germany under the number 01NVF17020. The Study has been registered in the German Clinical Trials Register under DRKS00014838 and was approved by the ethics committee of the University of Ulm on the 4th of August 2017 (covering the study sites: Ravensburg, Ulm, Neuruppin) According to state regulations of Lower Saxonia a separate ethics approval was needed for the study site Lueneburg, which was obtained on the 25th of October 2017 by the ethics committee of Lower Saxonia.

## Methods/design

CCSchool comprises the following three modules as part of a stepped-care model:Module A: standardized diagnostic procedure,Module B: School-based assessment followed by a first intervention (therapeutic assessment)Module C: School-based treatment.

There are two kinds of therapists working on one case: Responsible Therapists (RT) and CCSchool-Therapists (CCST).

The RT manages the case and decides which patients enter module A and may receive the treatment of the modules B and C in addition to module A. The role of the RT can be assumed by physicians, psychologists and other mental health professionals specializing in child and adolescent psychiatry/psychotherapy or paediatrics.

Eligible as CCSchool-Therapist (CCST) are occupational therapists, psychologists in training, social workers, nurses and other health professionals. The CCST will conduct the school-based assessment and the school-based interventions (modules B and C).

All of the participating therapists (RTs and CCSTs) have to complete an e-learning programme before being eligible to recruit or work with patients in CCSchool.

Students suspected of mental health problems associated with school problems, will undergo a screening for CCSchool. Students can be referred to the screening procedure either by (a) parents, (b) a paediatrician/child and adolescent psychiatrist/GP.

Inclusion criteria area psychiatric diagnosis andschool problems (academic or social) pointed out by the teacher or parents or high scores on the school-items of the Columbia Impairment Scale (CIS) filled-in by parents and/or students anda psychosocial functioning level on the Children Global Assessment of Functioning Scale (C-GAF) equal or below 70.

Exclusion criteria are: primary diagnosis of substance abuse or an issue of child protection that has to be addressed first.

Once found eligible for CCSchool, the parents and the child or adolescent will be informed about the study, and, if they are interested in participation, parents and child/adolescent will be asked to sign an informed consent form.

CCSchool will take place in about 20 administrative districts (with an average of 150.000 residents per district), which are evenly randomized into districts for recruitment of the intervention group and districts for recruitment of the control group. Not all health statutory insurances wanted to participate, resulting in about 60% of the children and adolescents in school being eligible for CCSchool. If a child is screened positive and is covered by an health statutory insurance which does not participate in general, the child can enter the contract individually and thereby become eligible for CCSchool.

Assuming hospitalization rates in the eligible population are about five times higher than national average due to the high selectivity (about 5.810 cases per 100.000 children and adolescents), the expected effect of CCSchool treatment will lead to a decline in admissions by 10% (which would then be 5.230 cases per 100.000 children and adolescents). A corresponding power analysis showed that the expected difference can be found when including 20 clusters (districts), with an average cluster-size of 90 patients and a coefficient of variation of k = 2.6 with a power of 90% and an alpha of 5%. Thus, CCSchool plans to recruit about 900 participants in the intervention and control group, respectively, who participate at least in module A. About 50% of subjects are expected to participate in module B and another 30% will be recommended to receive treatment in module C. According to power calculation, a sample of about 900 participants in each group is sufficient to find the expected effects.

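### The stated 90% power does not follow from its own inputs: 900 children per arm give about 8% power for 5.81% versus 5.23%

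*Protocol article*

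**What the plan says.** All inputs stand in the sample-size paragraph of the Methods/design section of the protocol article (the full stop is its thousands separator):

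- Control rate: "about 5.810 cases per 100.000 children and adolescents".
- Effect: "the expected effect of CCSchool treatment will lead to a decline in admissions by 10"%, giving the intervention rate, "which would then be 5.230 cases per 100.000 children and adolescents".
- Size: the difference is said to be detectable "when including 20 clusters (districts), with an average cluster-size of 90 patients".
- Remaining parameters: "a coefficient of variation of k = 2.6 with a power of 90% and an alpha of 5"%.
- Allocation: the districts are those "which are evenly randomized into districts for recruitment of the intervention group and districts for recruitment of the control group", so 10 per arm.
- Conclusion: "a sample of about 900 participants in each group is sufficient to find the expected effects".

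The Methods part of the Abstract gives the expected module A number (901) "according to power calculation". The Goals section makes inpatient admissions the primary outcome. The article does not define k, the sidedness of the test or the time unit of the rate.

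**The concern.** A 10% relative reduction from a rate near 6% is an absolute difference of 0.58 percentage points. Trials of 900 per arm do not normally detect differences of that size in an uncommon outcome. A coefficient of variation of 2.6 is also very large for a cluster trial, and a large value should push the required number of districts up.

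The primary question depends on this figure. The Discussion says the programme may become part of the regular statutory benefit scheme if it proves effective. If the true effect is the assumed 10%, more than nine in ten such trials would end without significance. A reader who believes the trial had 90% power could then take that result as evidence that the programme does not reduce admissions.

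**Working it through.** **Inputs** (all from Methods/design): p0 = 0.0581, p1 = 0.0523, d = p0 − p1 = 0.0058, n = 900 per arm, c = 10 districts per arm, m = 90 children per district, k = 2.6, alpha 5%. I treat the rates as the proportion hospitalised over the comparison period and the test as two-sided. Both are assumptions, and both are varied below.

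**Consistency of the effect.** 5,810 × 0.9 = 5,229, so 5,230 is correct for a 10% decline. Expected cases per arm: 900 × 0.0581 = 52.3 and 900 × 0.0523 = 47.1.

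**Best case, no clustering.**

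- Variance sum: 0.0581 × 0.9419 + 0.0523 × 0.9477 = 0.05472 + 0.04956 = 0.10429.
- Standard error: √(0.10429/900) = 0.01076, or 1.08 percentage points. The 95% confidence half-width is 1.96 × 1.076 = 2.1 points, against an assumed effect of 0.58.
- Standardised effect: 0.0058/0.01076 = 0.539.
- Power: Φ(0.539 − 1.96) = 7.8% in the beneficial direction, plus 0.6% in the wrong direction, 8.4% in all. One-sided at 5%: 13.4%.
- Children needed for 90%: (1.960 + 1.282)² × 0.10429/0.0058² = 10.507 × 0.10429/0.00003364 ≈ 32,575 per arm, and 32,575/900 ≈ 36 times the plan.

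**With clustering.** The Hayes–Bennett formula for unmatched clusters is

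c = 1 + (zα/2 + zβ)² × [p0(1−p0)/m + p1(1−p1)/m + k²(p0² + p1²)] / d².

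The binomial part of the bracket is 0.10429/90 = 0.001159, and p0² + p1² = 0.006111. Power comes from a cluster-level t-test with 10 districts per arm (18 df), counting both tails. The k = 0.25 row is for illustration only; the article does not give that value.

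| k | Bracket | Districts per arm for 90% | Power with 10 per arm |
|---|---|---|---|
| 0 | 0.001159 | 363 | 8.0% |
| 0.25 | 0.001541 | 482 | 7.3% |
| 2.6 | 0.042468 | 13,266 | 5.1% |

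**What k = 2.6 would mean as a between-district coefficient of variation.** The district standard deviation is 2.6 × 5.81 = 15.1 percentage points around a mean of 5.8%. The implied intracluster correlation is k²p0/(1−p0) = 6.76 × 0.0581/0.9419 = 0.417. The design effect is 1 + 89 × 0.417 ≈ 38, leaving an effective 900/38 ≈ 24 children per arm.

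**Other readings tried** (two-sided unless stated):

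- k misprinted for 0.26: 7.2%. For 0.026: 8.0%.
- k as the coefficient of variation of district size, with intracluster correlation from 0 to 0.05: at most 7.8%.
- k as an individual-level coefficient of variation: 12.6% (20.3% one-sided).
- 20 districts per arm instead of 20 in total, k = 0: 11.5% (18.5% one-sided).
- Poisson event counts over two years of person-time instead of one: 10.8%.

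None approaches 90%.

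**What the design can detect with 90% power.** Without clustering, a fall from 5.81% to about 2.72% (53%) by the normal approximation, or to about 2.58% (56%) with the 18-df t-test. At k = 0.25, a fall to about 2.23% (62%).

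**The case against.** The strongest objection concerns k. The article never defines it, and the phrase directly follows the average cluster size, so it could describe variation in district size. It may also be a misprint. The 5% power, the intracluster correlation of 0.42 and the design effect of 38 all depend on reading k as the between-district variation of the rate. That is fair, and those figures are conditional. The 8% figure is not: it sets clustering to zero, which is the most favourable case.

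The article also speaks of cases and admissions with no time unit, and one child may have several. Counting events over two years moves power only to about 11%. Under Control group, controls receive usual care for 12 months and may then enter the programme, so a longer randomised comparison is not available.

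The Evaluation and study analyses section plans adjusted longitudinal mixed models and matched external controls, not a crude two-proportion test. The 2.1-point half-width is therefore a crude, unclustered figure and not a strict bound for the planned model. The gap is still too large to close this way. A covariate correlated 0.9 with the outcome would multiply the standard error by √(1 − 0.81) = 0.436. The standardised effect becomes 0.539/0.436 = 1.24 and power about 24%. The power claim is tied to the randomised districts, and external controls do not enlarge the intervention arm.

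Finally, the article does not itself say that a null result would be read as no effect, and an effect well above 10% could be detected. Both points stand. They limit the consequence, not the arithmetic.

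**Conclusion.** The concern holds. The 90% power and the statement that 900 per group suffice are contradicted by the rates, cluster numbers and alpha given in the same paragraph. True power for the assumed 10% reduction is about 8% at best with two-sided testing (13.4% one-sided), and about 5% if k = 2.6 is the between-district coefficient of variation of the rate. The no-clustering figure takes the rates as risks over the comparison period and ignores dropout; loss of participants would lower it further. This is an error in figures the article states, not a detail left to a fuller document. It does not show that the intervention is ineffective, and it says nothing about power for the secondary outcomes.

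**What to change.** - Withdraw the 90% power statement and the sentence that about 900 per group is enough. Remove the appeal to the power calculation in the Abstract, or correct it to match.
- State what 10 districts of about 90 children per arm provide at a 5.81% control rate: about 8% power for a 10% reduction, and 90% power only for reductions above about 55% (about 62% if k were 0.25).
- Define k, justify its value from data, and give the formula, the sidedness and the time unit of the rate.
- Ask the sponsor for the original calculation, to establish whether the fault is a transcription slip in the article or an error in the design.

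It would also help to say that the admission result will be reported as an estimate with its confidence interval and that non-significance will not be taken as absence of effect. The correction does not depend on that addition.

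The cost is protocol wording and a less favourable published figure. No extra patients are needed.

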### Intervention group

If the patient attends a school that is located in an intervention group district, the following modules will be offered according to a stepped-care concept:

#### Module A

Module A is administered by the RT and comprises (1) a physical examination, (2) a standardised psychological assessment with the following questionnaires:Strengths and Difficulties Questionnaire (SDQ),Child Behaviour Checklist (CBCL),Youth Self Report Form (YSR) for children aged > 11 yand (3) evaluation of possible participation deficits, systematically assessed by conducting a half-standardized interview with the parents.

The diagnostic findings of module A will be summarized in a detailed clinical report. If the assessment result confirms a mental health diagnosis associated with manifest school problems and participation deficits the child or adolescent enters module B.

#### Module B

Module B includes (a) a school-based assessment as well as (b) a first intervention. The school-based assessment is carried out by the CCST, who observes the student in school assessing his/her social behaviour, ability to stay focussed, his/her learning behaviour in class as well as his/her behaviour during recess. The CCST fills in a standardized school assessment form based on these observations. The class-teacher will be asked to fill in the teacher report form (TRF), and the CCST will conduct a half-standardized interview with the class-teacher.

Once school assessment took place, the RT and CCST will invite the family, patient and possibly teacher to the office to discuss the results and offer therapeutic assessment (TA, a method by Ougrin et al., [26]) as first intervention. TA consists of a joint construction of a diagram (based on a cognitive analytic therapy paradigm) that consists of three elements: reciprocal roles, core pain and maladaptive behavioural patterns, which are each assumed to play a crucial role in setting off and promoting dysfunctional cycles of behaviour. The target problem is identified jointly. Motivation for change is considered and enhanced and then potential “exits” (i.e. ways of braking the vicious cycle of school failure/problems) are installed.

One week after TA, the RT sends an “understanding letter” to the child/adolescent, enhancing the identified alternative “exits”. Four weeks after TA the RT calls the family to ask if change has taken place. If this is not the case the child or adolescent will be offered module C.

#### Module C

Module C is offered in two forms:regular CCSchool-treatment (about 80% of subjects in module C should qualify for this setting): with four to six sessions in school within 3 months,intensive CCSchool-treatment (about 20% of subjects in module C should qualify for this setting) with 6 to 12 sessions in school within 3 months as well as optional phone calls between the sessions.

Goal attainment scaling will be used to monitor the process [27]. The methods of intervention to be used are not manualized. Instead the RT and CCST choose individually for each student those methods deemed appropriate for the goal to be reached according to goal attainment scaling. Possible interventions are: psychoeducation of teachers and/or parents, social competence training, conveying learning strategies or methods of staying focussed, installing CBT programs etc. The methods themselves and their effectivity are not the focus of this study and will not be evaluated. These are standard interventions. The query is more so, if the fact that they are applied in school will make a difference.

Assessment of quality of life (KIND-L), level of functioning (C-GAF), school absenteeism and level of impairment (CIS) will take place at four time points: At recruitment (T0), 6 months after recruitment or after completion of last module (which can be A, B or C) (T1), 12 months (T2) and 18 months (T3) after recruitment.

The steps of the study are summarized in Fig. 1.

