### Control group

The control group follows a waiting list design. Recruited children and adolescents, who attend school in a control group district, will receive treatment as usual (TAU) for 12 months. Level of functioning (C-GAF), level of impairment (CIS), quality of life (KIND-L) and days of school absenteeism will be recorded at recruitment (T1), as well as after six (T2) and 12 months (T3). After 12 months the parents and child/adolescent will be screened again for eligibility and – if still eligible - offered to enter the intervention part of the study and participate in module A as well as B and C if necessary. After an additional 6 months or after completion of module C the last assessment (T4) will take place.

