### Evaluation and study analyses

An external independent research institute (IGES Institute GmbH) will evaluate the achievement of the endpoints in CCSchool. The evaluation will use primarily data collected and assessed during the study on level of functioning, level of impairment, absenteeism and quality of life as well as data from documentation and process evaluation. In addition, claims data from the statutory health insurances will be analysed.

The study uses a cluster-randomized design with a waiting-list control group. Participating districts will be randomly assigned to an intervention and a control group. Children and adolescents, who are eligible for participation, will be allocated in the control versus intervention group depending on the location (district) of their school to avoid situations where there are intervention and control participants in the same school/class. The evaluation will compare the resulting intervention and control group participants on all outcome variables. In addition, claims data on the CCSchool participants as well as on children and adolescents with the same inclusion diagnoses (a) living in districts not included in the study and (b) living in the CCSchool districts before CCSchool has started (historical comparisons) will be analysed. These external control participants are matched to the intervention participants by propensity score matching. The claims data allows validating the self-reported data on hospitalization rates and analysing potential effects on health care costs.

The statistical analyses of the comparisons between randomized control group, external control group and intervention group will use a multilevel framework taking the cluster randomisation into account. Longitudinal regression analyses of changes in hospitalization rates, quality of life, symptoms and absenteeism are conducted using mixed models adjusting for potential confounders (e.g., age, gender, regional characteristics). This approach is feasible to estimate within-person changes over time as well as group differences in within-change over time. For process evaluation, cross-sectional group comparisons will be analysed with regression models without repeated measures and descriptive statistics. All effects will be tested with a significance level of *p* ≤ .05.

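### The intervention arm's first follow-up can fall at 6 months or at module completion, while the control visit is fixed at 6 months, so the 6-month contrast of secondary outcomes may compare different follow-up times

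*Protocol article*

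**What the plan says.** The intervention schedule stands at the end of the Module C section. Quality of life, functioning, absenteeism and impairment are assessed four times: "At recruitment (T0), 6 months after recruitment or after completion of last module (which can be A, B or C) (T1"), then "12 months (T2) and 18 months (T3) after recruitment". The text does not say whether the earlier or the later of the two T1 anchors governs, or who decides.

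The Control group section lists the same four measures, which "will be recorded at recruitment (T1), as well as after six (T2) and 12 months (T3"). These times are fixed. Controls "will receive treatment as usual (TAU) for 12 months" and, if still eligible, are then offered the intervention. "After an additional 6 months or after completion of module C the last assessment (T4) will take place".

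On the analysis, the Evaluation and study analyses section states: "The evaluation will compare the resulting intervention and control group participants on all outcome variables". It plans longitudinal mixed models of change over time. It names no time point for the randomised comparison and does not say how visits are matched.

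**The concern.** A between-arm comparison at a visit needs the visit to mean the same thing in both arms. Here the first follow-up has a second anchor, tied to treatment, in one arm only. If that anchor is used, elapsed time since recruitment differs by arm, and some intervention children are measured just as their last module ends, a moment with no counterpart among controls.

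The timing is also not random within the intervention arm. A child enters module B if module A confirms a diagnosis with school problems and participation deficits. In module B, "Four weeks after TA the RT calls the family to ask if change has taken place", and module C is offered if it has not. Visit time would thus follow severity and, for module C, lack of response.

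The affected measures carry two of the three research questions (participation and quality of life) and three of the four secondary outcomes. Since controls may start the intervention after month 12, only months 6 and 12 give a follow-up contrast against untreated controls. One of those two is exposed.

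**Working it through.** The plan gives no figure to reproduce on this point. The check sets the two schedules side by side and then asks how far T1 could move.

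**1. Visits in months since recruitment**

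| Month | Intervention label | Control label | Aligned? |
|---|---|---|---|
| 0 | T0 | T1 | yes |
| 6 | T1 (or module completion) | T2 | only if T1 is held at 6 months |
| 12 | T2 | T3 | yes |
| 18 | T3 | T4 (or completion of module C) | T4 floats, and eligible controls have been offered the intervention |

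Read by label instead, T1 is month 6 against month 0, T2 is 12 against 6, and T3 is 18 against 12: an offset of 6 months each time.

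**2. How many children end at each module** (expected numbers in the Abstract: A 901, B 428, C 103)

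- End at A: 901 - 428 = 473; 473/901 = 52.5%
- End at B: 428 - 103 = 325; 325/901 = 36.1%
- Reach C: 103; 103/901 = 11.4%

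**3. When the last module could end**

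Stated durations: the call comes 4 weeks (0.92 months) after the therapeutic assessment (TA), and regular module C runs "with four to six sessions in school within 3 months". Together they add up to 0.92 + 3 = 3.92 months after TA.

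Assumed, because the documents give neither: *a* = 0.5 to 3 months from recruitment to the end of module A, and *b* = 0.5 to 3 months from there to TA. Module B is taken to end with the 4-week call, and module C to use its full 3 months from that call.

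- A last: *a* = 0.5 to 3.0 months
- B last: *a* + *b* + 0.92 = 1.9 to 6.9 months
- C last: *a* + *b* + 0.92 + 3 = 4.9 to 9.9 months

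**4. T1 under each reading of the 'or'** (months; control visit always at 6)

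| Last module | Completion governs | Earlier of the two | Later of the two |
|---|---|---|---|
| A | 0.5-3.0 | 0.5-3.0 | 6 |
| B | 1.9-6.9 | 1.9-6.0 | 6.0-6.9 |
| C | 4.9-9.9 | 4.9-6.0 | 6.0-9.9 |

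Under the 'later' reading, children ending at A are on time. A child using the full 3 months of module C passes month 6 once TA comes more than 6 - 3.92 = 2.08 months after recruitment. Under these assumptions, no reading that uses the completion anchor keeps every child at 6 months.

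**The case against.** The strongest reply is that the damage is confined. Both arms are timed from recruitment, and months 0 and 12 match exactly. Month 12, which closes the treatment-as-usual period, is untouched. Inpatient admission does not appear in either assessment schedule. What remains is one interim visit of secondary outcomes. All of this stands, and it sets the severity.

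A reader might infer from the offset labels that every T1 to T3 contrast is shifted by 6 months. The documents do not support that. Nowhere are visits said to be matched by label, and the planned models describe change over time without naming a label. The offset could cause an error when the external institute merges the data, but it is not a planned mismatch.

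A reader might also take 473 of 901 as the number of mistimed visits. It is the expected number ending at module A. Whether any of them is seen early depends on how the 'or' is applied and how long module A takes, and neither is stated. The dependence on non-response is likewise limited to the gate into module C, expected for about 11% of the arm; entry to module B rests on diagnostic findings.

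Unequal counting windows for absenteeism are a possibility only, because no recall period is given. How time is coded in the mixed models is normally left to an analysis plan, which is not shown, so its absence is no fault here. Modelling actual dates would reduce the timing problem. It would not fully remove it, since visit time in one arm would still be tied to the treatment path. The visit rule itself is in the protocol, and it differs between arms.

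**Conclusion.** The point holds for the 6-month contrast of KINDL, C-GAF, CIS and absenteeism. As written, the schedule allows intervention children to be assessed at a time set by the module they reach, against controls assessed at a fixed 6 months. Under the assumed intervals, T1 could lie anywhere from about 0.5 to 9.9 months. These limits depend on two durations that the documents do not give, and the number of children affected is unknown.

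The 12-month contrast is unaffected, and no effect on the primary outcome is shown. The label offset and the floating control T4 are inconsistencies to tidy. The first shifts contrasts only if someone matches by label; the second falls after the randomised comparison against treatment as usual has ended. Severity: moderate.

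**What to change.** - Set the first follow-up at 6 months after recruitment, with the same window, for every child in both arms, whatever module was reached.
- Keep any end-of-module assessment as a separate process measure, outside the arm comparison.
- Use one set of month-based visit labels (0, 6, 12, 18) in both arms, and resolve the alternative anchor for the last control assessment.
- Analyse by time since recruitment, and name the time point of the randomised comparison.

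The cost is a short amendment and relabelled forms. Some children will need a questionnaire at 6 months in addition to, or instead of, the one at module end.
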